**Methods:**

Using Reach, Effectiveness, Adoption, Implementation, Maintenance (RE-AIM) and Proctor’s Implementation Outcomes Frameworks, this two-arm hybrid type-III cluster-randomized controlled trial (RCT) will compare two implementation strategies, VLC versus TA, among the 48 National Cancer Institute Community Oncology Research Program (NCORP) practice clusters that have not historically provided palliative care to all patients with advanced cancer. Three cohorts of practice clusters will be randomized to the study arms. Each practice cluster will recruit 15–27 patients and a family caregiver to participate in ENABLE. The primary study outcome is ENABLE uptake (patient level), i.e., the proportion of eligible patients who complete the ENABLE program (receive a palliative care assessment and complete the six ENABLE sessions over 12 weeks). The secondary outcome is overall program implementation (practice cluster level), as measured by the General Organizational Index at baseline, 6, and 12 months. Exploratory aims assess patient and caregiver mood and quality of life outcomes at baseline, 12, and 24 weeks. Practice cluster randomization will seek to keep the proportion of rural practices, practice sizes, and minority patients seen within each practice balanced across the two study arms.

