### Primary aim (implementation outcome, patient level)

Compare the effectiveness of VLC vs. TA on ENABLE program uptake, as measured by the proportion of patients who complete the ENABLE program (i.e., have a palliative care assessment and complete the six ENABLE sessions). *Hypothesis*: Practice clusters randomized to VLC will have greater ENABLE program uptake than practice clusters randomized to TA.

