### Aim 1: ENABLE uptake (implementation outcome, patient level)

The primary outcome will be *ENABLE program uptake* (program completion). To capture ENABLE program uptake, each ENABLE Nurse Coach will use a standardized ENABLE Nurse Coach Contact Log to document patient and caregiver referrals, enrollment, and completion of the essential ENABLE elements (i.e., palliative care assessment, ENABLE sessions). The Nurse Coach Contact Log, which is completed in REDCap, will document each contact and ENABLE session using an assigned study identification for each patient or caregiver.

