### Exploratory aim: patient measures

Table 2 presents patient measures. Patient assessments will be completed at baseline, 12, and 24 weeks. There will be several options to collect the data: [1] study coordinator reads the questions to the patient (either in person or on the phone) and enters the patient responses, [2] the patient completes the assessments in person with a study coordinator, or [3] the patient will take a paper copy home, complete it, and return it at either the next visit, via mail, or scan and email.

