### Randomization

This cluster-randomized trial will be carried out in 3 sequential cohorts of 8–20 practice clusters (4–10 per study arm) to reach the desired sample size of 48 practice clusters. Within each cohort, RCT arm assignment will occur after completion of all required study trainings, including the ENABLE training (Fig. 3). A minimization algorithm for group assignment with random initial start will be used to attempt to simultaneously balance the proportion of rural practices, practice sizes, and minority patients seen within each practice across the two RCT arms. The minimization algorithm will be generated using R software. Study team members and practice cluster members will not be blinded to group assignment or study hypotheses.

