#### Analysis for aim 1: Implementation outcome (patient level)

We will use a logit GEE model with exchangeable correlation structure (to account for clustering within practice) for the binary patient uptake indictor (“yes” if the patient completed a palliative care assessment and all ENABLE program sessions prior to the 12 week assessments and “no” if the patient is still alive but has not completed a palliative care assessment and all six ENABLE program sessions prior to the 12-week assessments), with the group assignment as the main predictor. Model-predicted outcome proportions, odds ratios, relative risks, and confidence intervals for these measures will be used for interpretation. Supplemental analyses using appropriate methods for clustered data will consist of between-group comparisons of the proportion of recruited patients who could not complete the ENABLE sessions due to illness or death, and the number of sessions completed among all patients recruited.

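### The primary outcome's completion window closes at the 12-week assessment, not on a fixed day; a fixed window from enrolment would be an almost free improvement

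*Protocol article*

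**What the plan says.** The protocol article words the time limit of the primary outcome in three ways.

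- **Abstract, Methods:** patients "receive a palliative care assessment and complete the six ENABLE sessions over 12 weeks". This is a nominal period with no stated start.
- **Primary aim:** patients "have a palliative care assessment and complete the six ENABLE sessions". No time limit is given.
- **Analysis for aim 1:** a success is a patient who "completed a palliative care assessment and all ENABLE program sessions prior to the 12 week assessments". A failure is a living patient who "has not completed a palliative care assessment and all six ENABLE program sessions prior to the 12-week assessments". Here the limit is an assessment.

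The section on patient measures schedules assessments at baseline, 12 and 24 weeks and offers three ways of collecting them. Two involve the study coordinator. In the third, "the patient will take a paper copy home, complete it, and return it at either the next visit", or by mail or scan.

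Completion is recorded at the practice: "each ENABLE Nurse Coach will use a standardized ENABLE Nurse Coach Contact Log", which "will document each contact and ENABLE session using an assigned study identification for each patient or caregiver". On blinding, the Randomization section says: "Study team members and practice cluster members will not be blinded to group assignment or study hypotheses". The limitations section adds that patients and caregivers do not know their practice's arm.

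**The concern.** A binary outcome that asks whether something was completed in time needs the same time for everyone. Under the analysis wording the clock stops when the 12-week assessment takes place. A patient assessed late gains weeks in which to finish session six, and one assessed early loses them. For a living patient who never does the assessment, the wording does not say plainly when the window closes.

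The event is also not independent of the people whose performance is being compared. Practice staff deliver the sessions, keep the log and help collect the assessment, and they know both the arm and the hypothesis. If assessments ran later in one arm, the arms would be compared over unequal time, and the uptake difference would be biased by whatever share of patients finish in the extra time. This is the only outcome for which the trial is powered.

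**Working it through.** **1. Do the wordings classify patients differently?** Take two hypothetical patients, reading the abstract as a limit of 12 weeks from enrolment and the analysis rule as referring to the actual assessment date.

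| Patient | Session six done | Assessed | Abstract | Analysis rule |
|---|---|---|---|---|
| A | week 13 | week 14 | failure | success |
| B | week 12 | week 11 | success | failure |

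The two rules agree whenever the assessment falls exactly at week 12. They part only when it slips.

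**2. The plan's own figure.** Inputs from the Sample size section: 24 clusters per arm, 12 assessable patients per cluster (288 per arm), ICC 0.05, alpha 0.01 (taken as two-sided), 80% power, reference proportion 0.52.

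- Design effect = 1 + (12 − 1) × 0.05 = 1.55.
- Effective size per arm = 288 / 1.55 = 185.8.
- Detectable difference with a t reference on 48 − 2 = 46 degrees of freedom: 0.177. The stated 0.18 is reproduced. With a continuity-corrected normal formula, 0.52 versus 0.70 needs 282 per arm, against 288 planned.

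No stated figure depends on the cut-off, so the fix changes none of them.

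**3. Illustration of what unequal timing would do.** These inputs are assumptions and are not in the article: around week 12, 1 to 3 percentage points of patients finish their last session per week, and mean assessment timing differs between arms by 2 weeks.

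- Spurious difference = 2 × 1 to 2 × 3 = 2 to 6 points.
- Share of the detectable difference = 2/18 to 6/18 = 11% to 33%.
- Standard error = √{[p(1 − p) + q(1 − q)] / 185.8}, with p = 0.52 and q = p plus the shift.
- Rejection rate from a noncentral t on 46 degrees of freedom, critical value 2.687:

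| Spurious difference | Standard error | Noncentrality | Null rejection (nominal 1%) |
|---|---|---|---|
| 0.02 | 0.0518 | 0.39 | 1.5% |
| 0.04 | 0.0517 | 0.77 | 3.4% |
| 0.06 | 0.0515 | 1.17 | 7.3% |

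**4. Sensitivity to the assumption.** Suppose instead that 2% to 10% of the remaining non-completers finish per extra week. A 2-week gap then shifts uptake by 0.48 × (1 − 0.98²) = 0.019 to 0.48 × (1 − 0.90²) = 0.091. The size is governed by inputs that the article does not supply.

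**5. Equal drift.** If assessments slip by the same amount in both arms and there is no true effect, both proportions rise together and the difference stays at zero.

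**The case against.** The best defence is that the wordings are compatible. Assessments are scheduled at week 12, so the analysis rule can be read as meaning the scheduled time point. On that reading the abstract and the analysis section agree, and a patient who skips the questionnaire still has a cut-off. Visit tolerances and the handling of missed assessments are details that an article leaves to the full protocol or analysis plan, so their absence here is no fault. This largely stands, and it is why the point concerns the choice of an event as the limit and not a missing tolerance. A tolerance would narrow the variation without removing it.

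A reader might infer that practices control the window. The article does not support that. The assessment has a scheduled week, take-home paper is one of three modes, the return date of a form need not be the assessment date, and patients, who are not told the arm, partly determine when forms come back. Practices can influence the timing; no more can be said.

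A reader might also infer from Table 2, which lists the contact log for months 1 to 15, that late enrollees are cut off early and scored as failures. That entry is the collection period of the instrument over the 15-month strategy, not a patient's window, and no end of enrolment is stated.

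Finally, nothing shows that timing would differ by arm. Technical Assistance calls are also monthly and cover similar progress topics, and better scheduling could make assessments more punctual instead of later. Even the direction is open.

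**Conclusion.** The point holds as a cheap improvement, not as a demonstrated error. The analysis rule closes the window of the primary outcome at an assessment event, while the abstract gives 12 weeks and the primary aim gives no limit. If assessments slip, or a living patient does not do one, the window varies or is unclear, and unblinded staff can influence it.

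The article does not support the stronger statement that the primary comparison is biased. That requires timing that differs by arm. Should it occur, a spurious 2 to 6 points would put null rejection at about 1.5% to 7% against a nominal 1%. Those figures rest wholly on an assumed 2-week gap and an assumed 1 to 3 points of patients finishing per week.

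**What to change.** Define uptake as the palliative care assessment and all six sessions completed within a fixed number of days from the patient's enrolment, the same for every patient. Matching the abstract's 12 weeks gives 12 × 7 = 84 days. Derive it from contact-log session dates, whether or not, and whenever, the 12-week questionnaire is done. Use this wording in the abstract, the primary aim and the analysis section, and show the assessment-date version as a sensitivity analysis.

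The cost is about one sentence. The log already documents each session per patient, so no new data collection is needed, provided that session dates are captured in it (an assumption to confirm). The downside is that some late completions become failures, so stated uptake may fall slightly.

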### Sample size

#### Aim 1: Implementation outcome (patient level)

The RCT is powered for the aim 1 outcome, ENABLE program uptake, defined as the proportion of patients who complete the ENABLE program. In determining the targeted sample size, we made the following assumptions: [1] an intra-class correlation coefficient (ICC) value of 0.05, [2] alpha of 1% (*α* = 0.01) and 80% power, [3] 20% enrolled patients for whom completion of ENABLE cannot be assessed due to death or becoming too ill to continue with participation, and [4] a proportion of patients completing ENABLE of 0.52 in prior studies. With 24 practice clusters per group and a minimum of 12 patients per practice cluster (down from 15 after 20% unable to assess completion), for a total of 288 patients per group, the detectable difference in ENABLE program uptake is 0.18 (OR = 2.06; RR = 1.33), a medium effect size.

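### The sample size drops patients who are alive but too ill to finish ENABLE, while the primary analysis counts them as non-completers, so the stated power belongs to a different analysis set

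*Protocol article*

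**What the plan says.** The protocol article describes the Aim 1 denominator in two places.

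- **Sample size, Aim 1.** One planning assumption is "20% enrolled patients for whom completion of ENABLE cannot be assessed due to death or becoming too ill to continue with participation". Both groups are removed, which leaves "a minimum of 12 patients per practice cluster (down from 15 after 20% unable to assess completion". "With 24 practice clusters per group" this is carried through "for a total of 288 patients per group". The other inputs are "an intra-class correlation coefficient (ICC) value of 0.05", alpha of 1%, 80% power and "a proportion of patients completing ENABLE of 0.52 in prior studies". The result is a detectable difference of 0.18 (OR 2.06, RR 1.33).
- **Statistical analysis, Aim 1.** The GEE outcome is yes for patients who complete the assessment and all sessions before the 12-week assessments. It is no "if the patient is still alive but has not completed a palliative care assessment and all six ENABLE program sessions" by that time. Only patients who die before completing fall outside yes and no.

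A supplemental analysis in the same paragraph compares the arms on "the proportion of recruited patients who could not complete the ENABLE sessions due to illness or death". It names illness as a reason for non-completion but does not take those patients out of the primary model.

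**The concern.** A living patient who stops because of illness is not assessable in the sample size section and a non-completer in the analysis section. The two sections therefore use different denominators and, in general, different expected completion proportions. The group is a realistic one: eligibility requires an expected survival of at least 6 months, and uptake is judged at 12 weeks, so some patients will probably be alive but too ill at that point.

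Two things are at stake. First, the power statement does not describe the outcome that will be tested. Second, if the sample size wording were followed when the data set is built, someone would have to decide who was too ill. Practice staff know their arm and the hypotheses, and they also complete the contact log that records the outcome. The denominator could then be shaped differently in the two arms.

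**Working it through.** **Inputs.** From the article: 24 practices per arm, 15 enrolled per practice, 20% set aside, ICC 0.05, alpha 0.01, reference 0.52, difference 0.18 (so 0.70 in the better arm). Assumed: a two-sided test. The article does not state sidedness, but one-sided 0.01 gives a detectable difference of 0.160 (pooled z), which does not fit.

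**Reproducing the plan's figure.**
- Design effect = 1 + (12 − 1) × 0.05 = 1.55.
- Effective n per arm = 288 / 1.55 = 185.8.
- At 80% power from 0.52, the detectable difference is 0.171 with an unpooled z (0.691; OR 2.06, RR 1.33, as stated) and 0.177 with t on 46 df, which rounds to the stated 0.18.
- At 0.52 versus 0.70, SE = √[(0.52 × 0.48 + 0.70 × 0.30) / 185.8] = 0.0497 and 0.18 / 0.0497 = 3.62. Power is 85% (z) or 82% (t, 46 df).

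The plan's arithmetic is sound for the set of 288 per arm.

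**Moving to the set in the analysis section.** Let i be the share of enrolled patients who are alive but too ill, and d = 0.20 − i the share who die before completing. Only d leaves the denominator:
- m = 15 × (1 − d) per practice and 24 × m per arm;
- design effect = 1 + (m − 1) × 0.05.

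*Reading A: 0.52 is among assessable patients.* The too-ill enter as no, so both proportions are multiplied by 1 − i/(1 − d) = 0.80/(1 − d).

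*Reading B: 0.52 already counts ill living patients as non-completers.* The proportions stay at 0.52 and 0.70, and only m changes.

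Worked example, i = 0.10:
- m = 15 × 0.90 = 13.5; n = 324; design effect 1.625; effective n 199.4.
- Under A, 0.52 × 0.80/0.90 = 0.462 and 0.70 × 0.80/0.90 = 0.622, a difference of 0.160. SE = 0.0493, ratio 3.25, power 75% (z).

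| Alive but too ill (i) | m | n per arm | Proportions under A | Power A, z / t | Power B, z / t |
|---|---|---|---|---|---|
| 0 (all deaths) | 12 | 288 | 0.520 vs 0.700 | 85% / 82% | 85% / 82% |
| 5% | 12.75 | 306 | 0.489 vs 0.659 | 80% / 76% | 87% / 84% |
| 10% | 13.5 | 324 | 0.462 vs 0.622 | 75% / 71% | 88% / 85% |
| 15% | 14.25 | 342 | 0.438 vs 0.589 | 70% / 66% | 89% / 86% |
| 20% (no deaths) | 15 | 360 | 0.416 vs 0.560 | 66% / 62% | 90% / 87% |

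All power figures use unpooled variance and two-sided alpha 0.01; t has 46 df.

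**Enrolment above the floor.** Under reading A with i = 0.10, 18 enrolled per practice gives m = 18 × 0.90 = 16.2 and 80% power (z). With 21 per practice, m = 18.9 and power is 84% (z) or 80% (t). With 29 practices per arm at 15 patients each, power is 84% (z) or 81% (t, 56 df). With i = 0.20 and 21 per practice, power is 76% (z).

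**The case against.** The strongest reply is that an attrition allowance in a sample size paragraph does not define the analysis set. The analysis paragraph does, and it is clear: every living non-completer is a no, and nobody has to judge illness. That stands. The primary outcome definition is usable as written, and the risk from unblinded staff arises only if the sample size wording is applied instead. The supplemental comparisons would also help to show any difference between arms in illness-related non-completion. Even so, the power figure was derived on the other set.

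A reader might infer that 0.52 and 0.18 belong only to the assessable-patient outcome, and hence that the trial no longer has 80% power. The article does not support this. It attributes 0.52 to prior studies without giving a denominator, and under reading B the planned analysis has more power than stated.

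It is also fair to say that 15 per practice is the floor. The article expects 15 to 27 patients per practice and allows up to 58 practices. As shown above, enrolment within that range can offset some or all of any loss. That eases the practical consequence but does not reconcile the two sections.

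Finally, a condensed article may leave detailed missing-outcome rules to a document not shown. Here, however, the article gives two treatments of the same patients that disagree, and nothing else in it settles which applies.

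**Conclusion.** The inconsistency is in the current text and concerns the primary outcome. The detectable difference of 0.18 at 80% power is correct arithmetic for a set that excludes both the dead and the too ill. The planned analysis excludes only those who die before completing. The figure carries over unchanged only if every one of the 20% is a death.

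The size and sign of the error cannot be settled from the article. At 15 enrolled per practice, with 5% to 20% of enrolled patients alive but too ill, power at the planned effect is 80% down to 66% (z), or 76% down to 62% (t), under reading A. It is 87% up to 90% (z), or 84% up to 87% (t), under reading B. These ranges rest on the assumed death/illness split, the two-sided test, and the same illness share in both arms. The point calls for reconciling the two sections and restating the power. It does not show that the trial is underpowered.

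**What to change.** - Keep the rule in the Aim 1 analysis section as the single primary definition: every living non-completer is a no, whatever the reason. It needs no judgement of illness by unblinded staff.
- Change the Aim 1 sample size paragraph so that only deaths before completion leave the denominator, and give the assumed share of such deaths.
- State whether the prior 0.52 was a proportion of all enrolled, all living or only assessable patients, and re-express it on the primary denominator if needed.
- Restate the detectable difference or the power on that basis, with the sidedness of alpha.
- Report an analysis that excludes the too-ill as a sensitivity analysis only.

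The cost is a revised sample size paragraph, a clarifying sentence in the analysis section and one re-run of the power calculation. The design does not change. The stated power may become somewhat less favourable.

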#### Analysis for aim 2: Service outcome (practice cluster level)

Analysis will compare VLC vs. TA on NCORP practices’ overall ENABLE program implementation measured by the ENABLE GOI. Due to the small sample size for this practice cluster-level outcome (24 VLC vs. 24 TA), rather than conducting formal inference testing, comparisons will be descriptive statistics and effect size measures.

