### Secondary aim (service outcome, practice level)

Compare the effectiveness of VLC vs. TA on practice clusters’ overall ENABLE program implementation. This will be assessed using the ENABLE General Organizational Index (GOI), which measures factors that influence institutional implementation of evidence-based practices. *Hypothesis*: Practice clusters randomized to VLC will have better overall ENABLE program implementation than practice clusters randomized to TA.

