### Aim 2: Overall ENABLE Program implementation (service outcome, practice cluster level)

This outcome will be measured for each practice cluster via phone interviews with Nurse Coaches and coordinators using the ENABLE General Organizational Index (GOI). This instrument was developed to assess factors that influence institutional implementation of the ENABLE program [38]. We previously adapted [38] the General Organizational Index (GOI) which measures fidelity to an evidence-based practice by assessing two key elements of implementation: individualization and quality improvement [64]. The GOI has been shown to have acceptable psychometric properties [39]. The ENABLE GOI structured interview guide covers 12 domains (program philosophy, eligibility/client identification, penetration, assessment, individualized initial palliative care treatment plan, individualized subsequent ENABLE contacts, supervision, process monitoring, outcome monitoring, quality assurance, and client choices regarding service provision) associated with successful implementation. ENABLE GOI assessments will occur at baseline, 6 months (± 8 weeks), and 1 year (± 8 weeks). After the phone interview, the interviewer [40] will score each domain on a Likert scale for a total range of 12–60. Moreover, interviews will be recorded and transcribed for qualitative analysis to augment quantitative assessment of this outcome.

Table 2 presents additional implementation measures, including RE-AIM, process outcomes for the study arms (VLC and TA), and ENABLE process measures.

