### Statistical analysis

All randomized practice clusters will be included in primary comparisons, according to their group assignment, and regardless of their degree of participation in the study. Primary data analysis will include descriptive statistics for baseline practice cluster characteristics, patient characteristics, and outcomes in each RCT arm. We will examine the balance between RCT arms with respect to baseline characteristics (e.g., age, sex, race, cancer type, stage) using effect sizes, such Cohen’s d and Cramer’s. Factors showing non-trivial imbalances between comparators will be used as adjusting covariates in the between-group comparisons. Analysis will be conducted using the latest versions of SAS and R.

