#### Analysis for exploratory aims (patient and caregiver outcomes)

##### Exploratory aim 1

To compare NCORP practices randomized to VLC or TA on patient and caregiver quality of life and mood, linear mixed models will be used to estimate differences in patient and caregiver outcome trajectories over the 24-week follow-up period. If necessary, a false discovery rate adjustment will be used to adjust for multiple exploratory inferences [69].

##### Exploratory aim 2

The association between ENABLE sessions and change in patient outcomes will be examined with linear mixed models. Adjusting covariates will include patient characteristics that may influence participation in sessions (e.g., sex, illness acuity, age). Linear mixed models will also be used to examine the association between GOI scores and patient outcomes.

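### The secondary comparison on GOI should be a prespecified baseline-adjusted difference with a confidence interval; 24 versus 24 practices is a reason to forgo a test, not an adjusted estimate

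*Protocol article*

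**What the plan says.** The protocol article, under Secondary aim (service outcome, practice level), states a directional hypothesis: "Practice clusters randomized to VLC will have better overall ENABLE program implementation than practice clusters randomized to TA".

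The measurement section for Aim 2 gives the schedule, "ENABLE GOI assessments will occur at baseline, 6 months (± 8 weeks), and 1 year (± 8 weeks"), and the scale: the interviewer "will score each domain on a Likert scale for a total range of 12–60".

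The analysis section for aim 2 gives its reason, "Due to the small sample size for this practice cluster-level outcome (24 VLC vs. 24 TA"), and its choice: "rather than conducting formal inference testing, comparisons will be descriptive statistics and effect size measures". It names no role for the baseline score and no time point.

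The opening of Statistical analysis has a general rule: "Factors showing non-trivial imbalances between comparators will be used as adjusting covariates in the between-group comparisons". Its examples are age, sex, race, cancer type and stage; GOI is not among them.

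Two other places bear on the point. Under Sample size, "The RCT is powered for the aim 1 outcome", and no precision or power figure is given for GOI. Under exploratory aim 2, "Linear mixed models will also be used to examine the association between GOI scores and patient outcomes".

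**The concern.** The hypothesis predicts a direction, but the analysis stops short of anything by which that prediction could be judged. The reason offered, the number of practices, bears on how much weight a p-value can carry. It does not bear on whether the difference should be estimated as precisely as the data allow, or shown with its uncertainty. If anything, few units make the interval more necessary.

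The baseline score is already scheduled for every practice, and adjusting for it is the cheapest source of precision available. The general rule does not secure this. It takes effect only after an imbalance is seen, whereas adjusting for a predictive baseline improves precision whether or not the arms happen to differ.

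At stake is how the only secondary aim is read. A single standardised difference from 24 versus 24 practices could be taken as the answer on implementation, with no sign that it is uncertain by more than half an SD either way.

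**Working it through.** The article gives no precision or power figure for GOI, so there is none to reproduce. Its only power figure is for uptake and does not enter here.

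**Inputs from the article:** 24 practices per arm; GOI total at baseline, 6 and 12 months.

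**Assumed, because the article does not give them:** correlation r between baseline and follow-up GOI (0.3 to 0.8); equal SD in the two arms, with results in SD units; no missing GOI; baseline GOI unaffected by the assigned strategy; two-sided 5% level (1% also shown).

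**Step 1. Unadjusted interval.** The standard error of the difference is √(2/24) = 0.289 SD. With 46 degrees of freedom t = 2.013, so the half-width is 2.013 × 0.289 = 0.58 SD.

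**Step 2. Adjusting for baseline (ANCOVA).** Residual variance is multiplied by 1 − r², and one degree of freedom is spent (45 df, t = 2.014). The half-width is 2.014 × 0.289 × √(1 − r²). The equivalent number of practices per arm without adjustment is 24/(1 − r²). The detectable difference at 80% power comes from the noncentral t.

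| Analysis | 95% CI half-width (SD) | Equivalent practices per arm | Detectable at 5% (SD) | Detectable at 1% (SD) |
|---|---|---|---|---|
| Unadjusted | 0.58 | 24 | 0.83 | 1.02 |
| Adjusted, r = 0.3 | 0.55 | 26 | 0.79 | 0.98 |
| Adjusted, r = 0.5 | 0.50 | 32 | 0.72 | 0.89 |
| Adjusted, r = 0.7 | 0.42 | 47 | 0.59 | 0.73 |
| Adjusted, r = 0.8 | 0.35 | 67 | 0.50 | 0.61 |

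**Step 3. Why the use of baseline should be fixed in advance.** If the effect size were computed on change from baseline, the variance would be multiplied by 2(1 − r), assuming equal SD at the two times. That factor is 1.4, 1.0 and 0.6 at r = 0.3, 0.5 and 0.7, against 0.91, 0.75 and 0.51 for ANCOVA. The half-width for change is 0.58 × √1.4 = 0.69, 0.58 × √1.0 = 0.58 and 0.58 × √0.6 = 0.45 SD. At r = 0.3, a change score is therefore less precise than ignoring baseline altogether.

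**Step 4. Chance baseline imbalance.** The standard error of a baseline difference between arms is also 0.29 SD. In an unadjusted follow-up comparison the expected carry-over is r times the baseline difference, not the whole of it. For a one-standard-error imbalance this is 0.3 × 0.29 = 0.09, 0.5 × 0.29 = 0.14 or 0.7 × 0.29 = 0.20 SD.

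**Step 5. Is a test worthwhile?** For a true difference of 0.5 SD at 5%, power by normal approximation is Φ(0.5/[0.289√(1 − r²)] − 1.96): 41% unadjusted, and 44%, 52% or 68% at r = 0.3, 0.5 or 0.7. Power for a moderate difference is low unless r is high.

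**The case against.** The best defence is that the choice is open and reasoned. The trial is powered for uptake only, the article says why GOI is treated descriptively, and step 5 supports caution: a test with roughly 40% to 50% power for a moderate difference would not be informative. At the 1% level used for the primary outcome it would be weaker still. This stands, and it is why the point does not ask for a significance test. The article also says that the GOI interviewer cannot be blinded, and no model removes that bias.

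Three stronger readings are tempting, and the article does not support them.

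- A reader might infer that the effect sizes will be unadjusted and the baseline thrown away. The aim 2 analysis is silent on this, and the general imbalance rule could reach baseline GOI. What can be said is that adjustment is not secured, because the rule is conditional and does not name GOI.
- A reader might infer that no interval will be given. Declining a test does not decline an interval, and an analysis plan that is not shown may supply one, along with the time point.
- A reader might infer that the trial cannot answer its secondary question. An effect size does estimate the contrast, and the qualitative joint display adds to it.

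Nor do the mixed models for GOI under exploratory aim 2 contradict the descriptive choice. Their outcomes are at patient level, so the argument from 24 versus 24 does not apply in the same way.

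Finally, baseline GOI is a score on implementing a programme that practices have yet to deliver. It may be low everywhere and predict little. In that case the gain is close to the r = 0.3 row.

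**Conclusion.** The point holds as a matter of method. The wording of the secondary hypothesis and its descriptive analysis do not match, and the reason given justifies less than it is used for. It supports not relying on a test; it does not support passing over a prespecified baseline-adjusted estimate with its interval.

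In size, the 95% half-width is 0.58 SD unadjusted and 0.55 to 0.35 SD adjusted, for r from 0.3 to 0.8. This depends wholly on r, which the article does not give, and on complete GOI data from all 48 practices. The primary comparison on uptake is unaffected. It is a modest, inexpensive improvement to the trial's only secondary aim.

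**What to change.** In the aim 2 analysis, prespecify a practice-level ANCOVA of the 12-month GOI total on arm and baseline GOI, or a repeated-measures model of the 6- and 12-month totals with baseline GOI as covariate. Name any further covariates in advance and keep them few, since there are only 48 units. Report the adjusted VLC minus TA difference at 12 months with its 95% confidence interval, presented as an estimate with no required significance test. Reword the secondary hypothesis as an estimation aim. Keep the descriptive domain scores and the joint display. If the full analysis plan already specifies this, the article's wording need only be brought into line.

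The cost is one small model on data already scheduled, with no extra measurement. The drawback is that the precision gain will be slight if baseline GOI turns out to be only weakly predictive.
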